***Study period***

Experiments 1 and 2 can commence at the same time. For Experiment 1, each subject will be followed for 14 months. Subjects in the 2-year myopic control studies will be returning for their final visit in the next 12 months. Assuming that the subjects required in Experiment 1 can be recruited in 12 months and 2 months to complete data collection, the study period will be at least 28 months (12+14+2).

For Experiment 2, each subject will be followed for 13 months. Assuming 6 months for subject recruitment, and 2 months for data collection, the study period will be 22 months (6+14+2). As the two experiments can be conducted concurrently, and allowing for delays (eg delays in recruitment or subject returning for data collection), the estimated study period will be at least 28 months (Table 5).

***Manpower***

We will require at least two examiners. A masked examiner for the cycloplegic examination at the data collection visits and an unmasked examiner for ortho-k fitting, i.e. two full time research staff (one project fellow and one research assistant (RA)*) will be needed. We will need an administrative staff to help with booking of patients, lens ordering, record keeping and data entries etc. Both research personnel must be experienced ortho-k practitioners.

(*Will convert this post to a MPhil position if the RA is interested in further study)

***Outputs***

At least two papers and three conference presentations

**Table 1. Data collection visits for Experiments 1 & 2.**

| Cycloplegic | Non-cycloplegic | Description | Remark |
| --- | --- | --- | --- |
| Phase I |  |  |  |
| I-0 |  | Baseline |  |
| [RS period: Weekly visits (for Group OKd subjects) to determine stabilization of Rx. Order new ortho-k/spectacles for the 3 groups of subjects for delivery at Visit I-1 (Rx for Group C and OKc should not be more than 1 month old)] | | | |
| I-1 |  | End of RS period in Phase I (3 days)  (*same visit as I-0 for Experiment 2 as there will be no RS period) | - Delivery of glasses for Group C and ortho-k lenses for Group OKc - Delivery of glasses for Group OKd and all subjects in Experiment 2 |
|  | I-3 | 3 (1 week) after commencing Phase I |  |
|  | I-6 | 6 months (1 week) after commencing Phase I | - Order new ortho-k lenses/spectacles based on updated Rx for the 3 groups of subjects for Visit I-7 where indicated |
| I-7 |  | 7 months (1 week) after commencing Phase I |  |
| Phase II |  |  |  |
| II-0 |  | Equivalent to Visit I-7 | - Glasses for Group C and ortho-k lenses for Group OKc (if deemed necessary) - Ortho-k lenses for Group OKd and all subjects in Experiment 2 |
| II-1 |  | End of RS period (3 days) |  |
|  | II-3 | 3 (1 week) after commencing Phase II |  |
|  | II-6 | 6 months (1 week) after commencing Phase II |  |
| II-7 |  | 7 months (1 week) after commencing Phase II |  |

RS - Rx-Stabilization

Group C – Control group in Experiment 1

Group OKc – Ortho-k subjects who will continue ortho-k lens wear for the whole experiment period in Experiment 1

Group OKd – Ortho-k subjects who will discontinue ortho-k lens wear in Phase I and resume ortho-k lens wear in Phase II in Experiment 1

**Table 2. Contact lens solutions and lens accessories used.**

| **Products** | **Brand** | **Supply per 7 months per subject** |
| --- | --- | --- |
| Disinfecting solution | Menicon Menicare Plus | 4 bottles |
| Daily cleaner | Menicon O2 Care | 4 bottles |
| Saline | AMO LensPlus Purite | 7 bottles |
| Enzymatic cleaner | Menicon Progent | 4 boxes |
| Artificial tears | Alcon Tears Naturale Free | 14 boxes |
| Lens cases | AMO lens cases | 7 pieces |

**Table 3. Inclusion criteria for new orthokeratology lens wear**

| Age | - 6-15 years of age on the date of recruitment |
| --- | --- |
| Refractive error Myopia  Cylinder | - Non-cycloplegic manifest refraction -  1.50DS and ≤ 4.50DS in manifest refraction - ≤ 3.00DC for axis 18030 or ≤ 1.00DC for other axes |
| Visual acuity | - Best corrected monocular logMAR visual acuity 0.10 or better |
| Ocular health | - Eyes straight at distance and near with best subjective correction - No abnormal ocular health - No ocular conditions which might affect vision or vision development (for example, cataract and ptosis) - No previous rigid contact lenses (including orthokeratology lenses) experience - No contraindications for overnight orthokeratology lens wear. |
| General health | - No systemic conditions which might affect the vision or vision development |
| Others | - No previous experience in myopic treatment (e.g. refractive surgery or progressive lens wear for myopic control) - Willing to wear orthokeratology lenses in accordance with the instructions from practitioner - Willing to follow up the protocol of the study |

**Table 4a. Examination procedures for all subjects**

|  | **Data collection** | | **Ortho-k aftercare** | **Visits in RS period** |
| --- | --- | --- | --- | --- |
|  | **Cycloplegic** | **Non-cycloplegic** |  |  |
| Ortho-k subjects | **** | **** | **** | **** |
| Control subjects | **** | **** | **--** | **--** |
| **Procedures** |  |  |  |  |
| 1. Habitual/Unaided VA |  |  |  |  |
| high contrast | UM | UM | UM | UM |
| low contrast | UM | UM | UM | UM |
| 2a. Subj  2b. Obj refraction | UM | UM | UM | UM |
| 3. Best corrected VA |  |  |  |  |
| high contrast | UM | UM | UM | UM |
| low contrast | UM |  |  |  |
| 4. Photo-biomicroscopy | UM | UM | UM | UM |
| 5. Medmont | UM | UM | UM | UM |
| 6. ORA | UM | UM |  |  |
| 7. Pentacam | UM | UM |  |  |
| 8. SP-2000P/ConfoScan 4 | UM |  |  |  |
| 9. Non-cyclo IOLMasterTM | M | M | M | M |
| 10. Cyclo IOLMasterTM | M |  |  |  |
| 11. Cyclo COAS | UM |  |  |  |
| 12a. Cyclo subj  12b. Obj refraction  12c. Peripheral Refraction | UM |  |  |  |
| 13. Cyclo Medmont | UM |  |  |  |
| 14. Cyclo Pentacam | UM |  |  |  |

UM: unmasked M: masked

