***Examiners***

One examiner (E1) will be responsible for lens fitting and monitoring the subjects and will therefore be involved in every visit. The masked examiner (E2) will be responsible for collection of the primary outcome measures, will be masked to the treatment received by each subject, and will only be involved in the data collection visits. Data entries and analysis will be made by another independent examiner (E3). E1 will also be masked to the AL measurements of each subject.

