***Examination procedures***

Table 4a and 4b list the test procedures and instruments used respectively in this study.

*Experiment 1*

The examiners will perform all test procedures including

- subjective
- objective refraction
- high/low contrast logMAR visual acuity assessment
- corneal topography
- slit-lamp biomicroscopy
- axial length measurement** (Cycloplegic and non-cycloplegic examination)
- corneal pachymetry
- non-contact intraocular pressure measurement
- corneal biomechanics assessment
- peripheral refraction (10° and 20°) (Cycloplegic examination)
- aberration (Cycloplegic examination)

Cycloplegia will be used on each subject at the cycloplegic data collection visits (0.5% alcaine followed by 1% tropicamide and 1% cyclopentolate).

**Only the masked examiner performs axial length measurements. Masked examiner will NOT perform any other procedures.

*Experiment 2*

Same as Experiment 1.

*Data collection visits*

Primary outcome measures will be determined in these visits, i.e. axial length. There are two types of data collection visits – cycloplegic data collection visits and non-cycloplegic data collection visits. The cycloplegic data collection visits are performed at the baseline, at end of the RS period, and 7 months after the beginning of each phase (see Figure 1 and Table 1). The cycloplegic data collection visit at the end of RS period will be conducted one week after stabilization of refraction has been achieved for OKd subjects in both Phases I and II in Experiment 1 and all ortho-k subjects in Phase II of Experiment 2.

The non-cycloplegic data collection visits are conducted every 2-3 months after RS period. In order to minimize the effect of diurnal variation, the data collection visits will be scheduled at about the same time of the day for each visit.

*Ortho-k aftercare visits*

For ortho-k subjects only. Regular ortho-k aftercare visits will be arranged upon delivery of ortho-k lens wear to ensure healthy and safe ortho-k lens wear. The ortho-k effect will be reviewed one night, one week, two weeks, three weeks, one month, and every 2-3 months after commencing lens wear. The weekly visits in the first month will only apply during the RS period.

- Commencement of lens wear. The night when the ortho-k treatment commenced/resumed. It shall be within 14 days after the last data collection visit.

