- The first overnight visit. The following morning after commencing lens wear. It is within 2 hours after waking and children should wear the lenses to our clinic.
- One week aftercare visit. Seven days ( 3 days) after commencing lens wear, 2 hours after waking.
- Two weeks aftercare visit. Fourteen days ( 3 days) after commencing lens wear, 2 hours after waking.
- Three weeks aftercare visit. Twenty-one days ( 3 days) after commencing lens wear, 2 hours after waking.
- One month aftercare visit. Twenty-eight days ( 3 days) after commencing lens wear. Can be in the morning or in the afternoon.
- The three monthly after care visits. It will coincide with the data collection visits.

*Visits during RS period (Group OKd in Experiment 1 and all subjects in Phase II in Experiment 2)*

Weekly ( 3 days) review of refraction, corneal shape and ocular conditions once the ortho-k treatment has stopped. It usually consists of 4-6 visits, depending on the initial refractive errors of the subjects. Refraction is considered stabilized when the change in refractive sphere and refractive cylinder in manifest refraction in two consecutive visits is 0.25 D or less and cycloplegic examination (cycloplegic data collection visit at end of RS period) will be arranged in the following week.

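### Row 9 of Table 4a sends the masked axial length examiner to aftercare and stabilisation visits that, in Experiment 1, identify Group OKd

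*Protocol*

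**What the plan says.** The Examiners section states that the masked examiner (E2), who collects the primary outcome, "will be masked to the treatment received by each subject, and will only be involved in the data collection visits". The Examination procedures section names axial length as the primary outcome, ties it to the data collection visits, and adds: "Only the masked examiner performs axial length measurements. Masked examiner will NOT perform any other procedures". The Examiners section also masks the fitting examiner (E1) to axial length.

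Table 4a has four visit columns: cycloplegic data collection, non-cycloplegic data collection, ortho-k aftercare, and visits in the RS period. Its key reads "UM: unmasked M: masked". Row 9 reads "9. Non-cyclo IOLMasterTM | M | M | M | M". In the line for control subjects, the aftercare and RS columns hold a dash.

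On attendance, the Examination procedures section describes aftercare visits as "For ortho-k subjects only" and heads the other set "Visits during RS period (Group OKd in Experiment 1 and all subjects in Phase II in Experiment 2". The Experiment 1 text says that Groups C and OKc have no RS period.

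**The concern.** Experiment 1 relies on E2 not knowing which treatment a child is on when reading axial length. Row 9 would place E2 at visits that only some children attend, so presence at such a visit discloses the group. This touches the randomised contrast, OKc against OKd, as well as the contrast with the non-randomised spectacle controls.

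Timing adds to the problem. Experiment 1 compares axial length change over the six months after refraction has stabilised. RS visits come before that window, so E2 could know a child's group before taking the reading from which change is measured.

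**Working it through.** No arithmetic applies. The check compares, for each kind of visit in Experiment 1, who attends, whether the text allows E2 to be there, and what row 9 asks for.

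| Visit | Who attends in Experiment 1 | E2 allowed by Examiners section? | Row 9 |
|---|---|---|---|
| Cycloplegic data collection | All groups (but see step 5 on I-1 and II-1) | Yes | M |
| Non-cycloplegic data collection | All groups | Yes | M |
| Three-monthly aftercare | Ortho-k children; coincides with data collection | Yes, as data collection | M |
| Overnight and weekly aftercare | OKd only, on resuming wear in Phase II | No | M |
| Weekly RS visits | OKd only | No | M |

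1. **Can someone else take the row 9 readings?** No. "Only the masked examiner performs axial length measurements", and E1 is masked to the results. An M in those columns can only mean E2.

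2. **Is row 9 just a table that does not separate visit types?** No. Rows 6 to 8 and 10 to 14 leave the aftercare and RS columns empty, so the table does distinguish them. Row 9 is the only row coded M that extends into them.

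3. **Does the visit description support an RS reading?** No. The text on RS visits lists refraction, corneal shape and ocular condition, and does not mention axial length.

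4. **Who is revealed, and when?** The weekly aftercare visits of the first month are limited by the text to the RS period, which Groups C and OKc do not have. The overnight visit follows the night on which lens wear starts or resumes. In Experiment 1 only OKd resumes wear, and the child arrives with the lenses in. The protocol expects 4 to 6 RS visits. On resuming wear it schedules one overnight visit, three weekly visits and a one-month visit; the last may coincide with II-1. An OKd child would thus meet E2 several times outside data collection, mostly before the I-1 or II-1 reading.

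5. **Would removing the two entries be enough?** Not necessarily. The Group OKd part of the Experiment 1 text says that the cycloplegic collection at the end of RS is for OKd alone. The part on Groups C and OKc says that their data collection visits match those of OKd, and Table 1 has glasses and lenses delivered to those groups at I-1. If the first statement governs, attendance at I-1 and II-1 would itself identify OKd.

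6. **Which experiments are affected?** The masking consequence belongs to Experiment 1. In Experiment 2 every child follows the same treatment sequence, so attendance does not separate treatment groups. The conflict between table and text remains there too.

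**The case against.** The strongest reply is that the text is consistent throughout and only the table departs from it. Three places (the Examiners section, the account of data collection visits and the account of RS visits) point to axial length at data collection visits only. On that view row 9 holds stray entries and no unmasking would occur. The aftercare M is also partly legitimate, since three-monthly aftercare falls on data collection visits. Both points stand: loss of masking is conditional on staff following the table. But a procedures table is what clinic staff work from, and the three-monthly overlap cannot explain the RS column.

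A reader might draw several stronger conclusions that the document does not support:

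- **That this is the trial's only masking.** E1 is masked to axial length, and data entry and analysis go to a separate examiner.
- **That the potential bias can be sized** by setting the 0.02 mm tolerance for a set of readings against half of the 12-month 0.12 mm difference, that is 0.06 mm. Halving assumes a linear effect, while the Introduction says that the effect was greatest in the first six months. The 0.02 mm is a repeatability limit for cycloplegic readings (row 10) and not a measure of bias. The cycloplegic rule also takes the first qualifying set, which limits selection. The non-cycloplegic rule, which would govern row 9, is still left open.
- **That correcting row 9 guarantees full masking.** Step 5 shows an unresolved conflict over I-1 and II-1, and nothing in the protocol says that E2 is shielded from visible spectacle wear at shared visits.
- **That the Manpower section gives E2 the whole cycloplegic examination**, from "A masked examiner for the cycloplegic examination at the data collection visits". This is loose staffing wording. Axial length is measured under cycloplegia at those visits, and the Examination procedures section expressly bars E2 from other procedures.

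**Conclusion.** The contradiction is certain. Row 9 of Table 4a requires E2 at RS visits and at the overnight and weekly aftercare visits, and the Examiners section excludes E2 from them. If the table is followed, every OKd child in Experiment 1 who attends these visits becomes identifiable to the primary outcome assessor, against both Group C and OKc, before the post-stabilisation window. With 80 ortho-k children recruited, that is about 40, assuming that all are randomised and split equally; the protocol does not state the allocation ratio. The conclusion that masking is lost rests on E2 recognising the child or the visit type, which is likely at weekly visits and more so when a child arrives wearing lenses. How far any reading would shift cannot be derived from the document, and the case for correction does not depend on it.

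**What to change.** Delete the M from the ortho-k aftercare and RS-period columns of row 9 in Table 4a, so that axial length is measured only at the scheduled data collection visits. Three-monthly aftercare visits that coincide with these remain covered by the data collection columns.

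Reconcile the two statements in the Experiment 1 text about the end-of-RS collection, so that the I-1 and II-1 axial length visits are held for all three groups and attendance does not itself mark a child as OKd.

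The first change is an edit to two table cells and reduces workload. It gives up axial length readings during RS and early aftercare, which the stated comparison of change after stabilisation does not use. The second costs nothing if all groups were already meant to attend. If not, it adds up to two visits for each child in Groups C and OKc.

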**Table 4b. Instrumentation**

| **Procedures** | **Instrument** |
| --- | --- |
| Habitual/Unaided VA | ETDRS charts (Precision Vision, IL, US) 100% contrast |
| Subjective refraction | Retinoscopy, trial frame and trial lenses and cross-cylinder |
| Objective refraction | Shin-Nippon Open Field Autorefractor |
| Best corrected VA | ETDRS charts (Precision Vision, IL, US) |
| Corneal biomechanics | Ocular Response Analyser (ORA) (Reichert Inc, Depew, NY) |
| Noncontact IOP | Nidex auto non-contact tonometer NT4000 |
| Corneal thickness | Pentacam (Oculus, Inc., Lynnwood, WA) |
| Corneal morphology | SP-2000P (Topcon, Tokyo, Japan)  ConfoScan 4 (Nidek, Inc., Freemont, CA) |
| Corneal topography | Pentacam (Oculus, Inc., Lynnwood, WA)  Medmont E300 (Medmont International Pty Ltd, Australia) |
| Photo-biomicroscopy | TOPCON TRC-NW6S and TOPCON IMAGEnet |
| Amplitude of Accommodation | Push-up bar |
| Cycloplegic axial length measurement | Zeiss IOLMasterTM (Zeiss Humphrey, Dublin, CA, USA) |
| Cycloplegic objective refraction | Shin-Nippon Open Field Autorefractor |
| Cycloplegic subjective refraction | Trial frame and trial lenses and cross-cylinder |
| Cycloplegic Aberrometry | Complete Ophthalmic Analysis System (COAS, Wavefront Sciences Ltd, USA) |

**Table 5. Study progress**

| **Months** | **1-4** | **5-8** | **9-12** | | | **13-16** | **17-20** | **21-24** | **25-28** |
| --- | --- | --- | --- | --- | --- | --- | --- | --- | --- |
| **Experiment 1** |  |  |  | | |  |  |  |  |
| * Recruitment |  |  |  | | |  |  |  |  |
| * Monitoring |  |  |  | | |  |  |  |  |
| **Experiment 2** |  |  |  | | |  |  |  |  |
| * Recruitment |  |  |  |  |  |  |  |  |  |
| * Monitoring |  |  |  | | |  |  |  |  |
| * Data collection |  |  |  | | |  |  |  |  |
| **Experiment 3** |  |  |  | | |  |  |  |  |
| * Recruitment |  |  |  | | |  |  |  |  |
| * Monitoring |  |  |  | | |  |  |  |  |
| * Data collection |  |  |  | | |  |  |  |  |

**Supplementary to Table 4a.**

| **Manufacturer of lenses** | **Menicon** | | **Procornea** | |
| --- | --- | --- | --- | --- |
| **Groups** | **Ortho-k** | **Control** | **High Myopes** | |
| **Procedures** |  |  |  |  |
| 1. Habitual/Unaided VA | Unaided | Habitual | Habitual | |
| LCD high contrast | **** | **** | **** | |
| High contrast EDTRS | **** | **** | **** | |
| Low contrast EDTRS | **** | **** | **** | |
| 2a. Subjective Rx | LCD chart + normal room lighting | | | |
| LCD high contrast | **** | **** | **** | |
| 2b. Obj refraction | - Shin-Nippon; Binocular fixation; Auto mode - 3 sets of readings; both sphere and cylinder not exceed 0.25D | | | |
| 3. Best corrected VA | Aided | | | |
| high contrast | **** | **** | **** | |
| low contrast | **** | **** | **** | |
| 4. Photo-biomicroscopy | List of graded items:   - Efron’s scale - Corneal staining: location / coverage / depth - Limbal, conjunctival, papillary injection: location / grade - Conjunctival staining: location / grade - Papillae and follicles: location / grade - Ortho-k related findings: iron ring, white lesion, fribrillary lines (presence/absence; grading) - Photo-documentation   - 16 standard photos for each eye     - Cornea and bulbar conjunctival x 5 gazes (central, inferior, superior, temporal and nasal)       - 5 locations x white light (diffuse light) @ 16X       - 5 locations x blue light (broad beam) @ 16X     - Iron ring (or the absence)       - 1 location x white light (parallelepiped) @ 16X       - 1 location x blue light (broad beam) @ 16X     - Palpebral conjunctiva for upper and lower eyelid       - 2 locations x white light (diffuse light) @ 16X       - 2 locations x blue light (broad beam) @ 16X   - Higher magnification and optic section for special features (appearance and depth) e.g. | | | |

**Supplementary to Table 4a (cont.)**

|  | **Menicon** | | **Procornea** |
| --- | --- | --- | --- |
|  | **Ortho-k** | **Control** | **High Myopes** |
| **Procedures** |  |  |  |
| 5. Medmont | - Cyclo visits: 4 good images per eye - Other visits: two good images per eye | | |
| 6. ORA | - 4 good images per eye:   - image score > 3.6 - perform NCT (TOPCON, 3 readings with difference not exceeding 3 mmHg) only if 3 good results cannot be obtained in 12 trials | | |
| 7. Pentacam | - 25 scans/s; 3 good images per eye | | |
| 8. SP-2000P/ConfoScan 4 | - Central: 3 images; CCT not exceed 10 um - Superior / inferior: 1 image | | |
| 9. Non-cyclo IOLMasterTM | - To be determined | | |
| 10. Cyclo IOLMasterTM | - AL: the first set of 5 readings within 0.02mm - ACD: 3 readings within 0.04mm | | |
| 11. Cyclo COAS | - Monocular fixation; central: 5 readings | | |
| 12a. Cyclo subjective Rx | - LCD chart + normal room lighting | | |
| 12b. Cyclo objective Rx | - Shin-Nippon; Binocular fixation; Auto mode - 3 sets of readings; both sphere and cylinder not exceed 0.25D | | |
| 12c. Peripheral Refraction | - Pupil alignment method - manual mode - quick 5 x 2: 5 out of 10 data will be used   - sphere and cylinder not exceed 0.50D;   - axis not exceed 30 degrees | | |
| 13. Cyclo Medmont | **** | **** |  |
|  | - 4 good images per eye | | |
| 14. Cyclo Pentacam | - 25 scans/s; 3 good images per eye | | |

Pertinent data will be determined for both eyes:

* 1-6, 9-10, 12a and 12b

For the other tests (11, 12c, 13-14)

* ROMIO and TO-SEE will continue to perform tests on both eyes

* Only eligible eye will be assessed for HM-PRO
